### Statistical Analysis

Data will be collected in the Castor online database. Patient characteristics will be described using descriptive statistics and tested for normality (using both the shapiro-wilk test and a visual evaluation of the histograms). A per protocol analysis will be used. Baseline characteristics between groups will be compared with the unpaired student's T-test for normally distributed data, Mann-Whitney U for not normally distributed data and Chi-squared test for proportions. Differences before and after the control or exercise period will be analyzed using a paired T-test for normally distributed data and Wilcoxon signed ranks test for not normally distributed data. If possible, missing outcome data will be imputed using multiple imputation. Statistical analyses will be performed using SPSS or R software. The significance level is determined at *P* < 0.05.

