### Randomization

Randomization will be performed in blocks of 4,6 using Castor. All children will be randomized in group A or group B. Group A will start with the tailored intervention after a control period of 6 weeks. Group B will start the tailored intervention immediately after the first measurement moment. Group A serves as controls for the whole group (with a 2:1 ratio) as group A does not have a washout period. Blinding of participants and physiotherapists to allocation is not possible due to the nature of the intervention.

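### The only between-group tests are of baseline characteristics; outcomes get before/after tests within each period, so group A's control period enters no outcome comparison

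*Protocol article*

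**What the plan says.** All references are to the protocol article.

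- **Randomization.** Children are randomised to A or B. "Group A will start with the tailored intervention after a control period of 6 weeks", and "Group B will start the tailored intervention immediately after the first measurement moment". The control role is explicit: "Group A serves as controls for the whole group (with a 2:1 ratio) as group A does not have a washout period".
- **Outcome Measurements and Sample Size Calculation.** The primary outcome is change in peak VO2. Each disease group is sized separately for a 5% rise, with 80% power, alpha 0.05 and an SD of 2.19.
- **Statistical Analysis.** Between groups: "Baseline characteristics between groups will be compared with the unpaired" t-test where the data are normal, with Mann-Whitney U and chi-squared tests as alternatives. For outcomes: "Differences before and after the control or exercise period will be analyzed using a paired T-test for normally distributed data", with the Wilcoxon signed ranks test otherwise. No other comparison is named, and *groups* is not defined.

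**The concern.** The design and the analysis answer different questions. Randomising the start of training gives a concurrent untrained group, which protects against growth, learning on the exercise test, season and regression to the mean. A paired test within the exercise period has none of that protection. Nor does finding the exercise change significant and the control change non-significant show that the two differ.

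The one place where the plan does compare groups is where a test is least useful. If *groups* means A and B, randomisation makes any baseline difference a chance one, and a non-significant P value in samples this small does not show balance. If it means the four diseases, an unpaired t-test or Mann-Whitney test handles two groups, not four. The sentence needs correcting on either reading.

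At stake is whether the trial can attribute a gain in peak VO2 to the training at all.

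**Working it through.** **1. What each named test compares**

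| Test | Compares | Uses group A as control? |
|---|---|---|
| Unpaired t, Mann-Whitney, chi-squared | Baseline characteristics, between groups | No outcome involved |
| Paired t, Wilcoxon signed ranks | Before v after, within one period | No |

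Nothing compares change under training with change in group A's control period.

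**2. Reproducing the sample sizes.** One-group formula, two-sided: n = (2.19 × (1.960 + 0.842) / δ)², with δ = 5% of the stated mean.

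| Disease | Mean | δ | n computed | n stated |
|---|---|---|---|---|
| Fontan | 27 | 1.35 | 20.66 → 21 | 21 |
| BPD | 39 | 1.95 | 9.90 → 10 | 10 |
| Pompe | 37.7 | 1.885 | 10.59 → 11 | 10 |
| IBD | 36 | 1.80 | 11.62 → 12 | 12 |

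Three figures match and Pompe is one short. The sizes are therefore those of a before/after test without a control, and 2.19 is used as an SD of change, although the text does not say which SD it is.

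**3. Power of the comparison that the design implies.** Assumptions: 2.19 is the SD of change, and the stated evaluable numbers split about 1:1. SE = 2.19 × √(1/a + 1/b); power ≈ Φ(δ/SE − 1.96).

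| Disease | a v b | SE | δ/SE | Power (normal) | Power (t) | Per arm for 80% |
|---|---|---|---|---|---|---|
| Fontan | 10 v 11 | 0.957 | 1.41 | 29% | 27% | 42 |
| BPD | 5 v 5 | 1.385 | 1.41 | 29% | 24% | 20 |
| Pompe | 5 v 5 | 1.385 | 1.36 | 27% | 22% | 22 |
| IBD | 6 v 6 | 1.264 | 1.42 | 30% | 25% | 24 |

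Pooling the 53 evaluable children (21 + 10 + 10 + 12) as 26 v 27 gives SE = 2.19 × √(1/26 + 1/27) = 0.602. A common effect of 1.35 then has power Φ(2.24 − 1.96) = 61%, and one of 1.95 has Φ(3.24 − 1.96) = 90%. This assumes one effect across four diseases whose interventions may differ.

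**4. What the baseline tests can show.** Power to detect an imbalance of half an SD is 19% (Fontan, 10 v 11), 11% (BPD and Pompe, 5 v 5), 12% (IBD, 6 v 6), and 55% with all 72 children as 36 v 36.

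**5. What baseline adjustment adds.** The documents give no between-child SD of peak VO2; 3-8 ml/kg/min is an assumption. With r = 1 − 2.19²/(2 × SD²):

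- SD 3: r = 0.734; variance of the adjusted analysis relative to change scores = (1 + r)/2 = 0.867, a saving of 13%.
- SD 8: r = 0.963; ratio 0.981, a saving of 2%.

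If changes were compared between arms without adjustment, a one-standard-error baseline imbalance would shift the result by (1 − r) × SD × √(2/n):

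- 7 per arm (one disease of 14): 0.43 (SD 3) to 0.16 (SD 8) ml/kg/min, that is 8-23% of the BPD and Pompe targets.
- 36 per arm (all diseases): 0.19 to 0.07 ml/kg/min.

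**The case against.** **Imbalance and the planned tests.** A reader might infer that a chance imbalance in baseline peak VO2 biases the planned outcome analysis. The document does not support that. The planned tests are within-child, so each child's baseline is already subtracted, and no A/B outcome comparison exists to carry an imbalance. This objection stands.

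**Size of the adjustment gain.** With 7 per arm and the assumed SDs, a one-standard-error imbalance in level is 3 × √(2/7) = 1.6 to 8 × √(2/7) = 4.3 ml/kg/min. Setting that beside a target change of about 1.9 overstates the matter: on the change scale it shrinks to 0.16-0.43. A larger variance saving could be claimed only against an analysis of follow-up values alone, which the plan never proposes. This also stands.

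**Chance findings.** A reader might expect several spuriously significant baseline differences. The article does not list the characteristics to be tested, so no number can be given, and no later step in the plan depends on these tests.

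**Level of detail.** Covariates are commonly left to an analysis plan, and this is a condensed article. That is fair for the covariates. It does not excuse the rest: the article affirmatively states how outcomes are tested, and that statement leaves out the control that the Randomization section sets up.

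**A kinder reading.** The paired test might be meant to compare each group A child's control change with the same child's training change. The wording pairs before with after. Even so, control always comes first in group A, and group B has no stated control period, so that contrast would not be the randomised one.

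**Conclusion.** The concern holds in this form: the stated analysis answers a weaker question than the design allows, because the randomised control period enters no outcome test, while the only between-group tests are uninformative baseline ones. This should be changed.

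It follows from the text alone that the comparison is missing. That the sample sizes belong to a one-group before/after test follows from the arithmetic, with Pompe one child short. The per-disease power of about 27-30% (22-27% by the t-test) rests on 2.19 being the SD of change and on a roughly equal split; the article states no allocation ratio and no stratification by diagnosis. The 2-13% variance saving rests on the assumed between-child SD of 3-8.

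Absence of baseline adjustment is secondary. Adding a covariate would not by itself repair the plan; adding the comparison would.

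**What to change.** 1. Drop the baseline significance tests. Describe baseline by arm and by diagnosis, and say what *groups* means.
2. Make the primary effectiveness analysis a between-arm comparison of peak VO2 after group B's training period with peak VO2 after group A's control period: a linear model with arm, baseline peak VO2 and diagnosis. Use the same form for continuous secondary outcomes.
3. If group A's later training period is also used, which is how the 2:1 ratio reads, fit a mixed model with a random child effect. Group A children then appear on both sides, and a plain linear model would treat their rows as independent.
4. Keep the paired before/after results as description.
5. Restate the power for this comparison, per disease and pooled.

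**Cost.** Mainly analysis wording; baseline peak VO2 and diagnosis are already collected. Baseline (one term) and diagnosis (three) spend four degrees of freedom. The analysis needs a measurement at the end of group A's control period; Study Design gives group A two visits plus a follow-up moment and group B three visits, which should be reconciled with the Randomization section.

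**What it does not solve.** The control period is 6 weeks against 12 weeks of training, so the arms are compared after different intervals; adjustment cannot remove that, and it should be stated as a limitation. Per-disease conclusions will remain imprecise at the planned sizes.

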## Methods and Analysis

### Study Design

This study is a prospective single-center randomized cross-over controlled trial. Eligible patients will participate in the 12-week tailored exercise intervention and are either randomized to start with a control period or start with the intervention. The tailored 12-week exercise interventions will be designed based on the found limitations for physical activity in each disease group during baseline measurements and previously published studies. Effects of the tailored exercise interventions will be measured on the following endpoints: exercise capacity (measured by cardiopulmonary exercise test), endurance, physical activity levels, muscle strength, quality of life, fatigue, fear for exercise, disease activity, cardiac function (in children with a Fontan circulation), energy balance, and body composition. Figure 1 shows the study design, visits, and measurements. The study includes two identical visits and a follow-up moment for group A and three identical visits for group B. Each visit consists of two assessment days with at least 3 days and maximal 7 days in between. All measurements will take place at the Erasmus MC—Sophia Children's hospital, the Netherlands. The study will be performed in accordance with the Declaration of Helsinki. It was approved by the local Ethics Committee of Erasmus MC Medical Centre (NL.70912.078.19) and registered at www.trialregister.nl as Trial NL8181.

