**Figure 2 F2:**
[figure not shown]
Design process and content of the tailored exercise intervention. MIP, Maximal inspiratory pressure; min, minutes; HIIT, high intensity interval training; HR, heart rate; VT2, ventilatory anaerobic threshold; REE, rest energy expenditure; kg, kilograms.

All children will participate in two or three supervised training sessions a week for 12 consecutive weeks. The most fitting form of physical exercise will be determined based on the consult with the sports physician in combination with the outcomes of the Maximal CPET, muscle strength measurements and core-stability measurements and measured maximal inspiratory pressure. Naturally, all previously published studies regarding exercise in the specific disease group will be taken in consideration when designing the tailored exercise intervention. When, for example, a certain training type has already been proven to be ineffective, this type of training will not be added to our tailored exercise intervention.

If a patient group shows a decreased PeakVO_2_ of <80% of predicted during baseline measurements, personalized aerobic training will be added to the exercise intervention consisting of 3 training sessions a week in heartrate zones: 2 (80–90% of HR at VT2) for 20 mins, 3 (90–95% of HR at VT2) for 3 × 5 mins and 4 (95–100% of HR at VT2) for 5 × 2 mins. If a patient group does not show a decreased PeakVO_2_ of <80% of predicted, personalized HIIT in heartrate zones 4 (95–100% of HR at VT2) and 5 (>100% of HR at VT2) will be added to the tailored intervention. Depending on measured muscle strength of the patient groups during the baseline measurements, muscle endurance exercises, high weight resistance exercises or body-weight and flexibility exercises, will be added to the program.

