### Outcome Measurements

#### Primary Study Outcome

Exercise capacity: Change in peak oxygen uptake (peak VO_2_), will be measured by maximal cardiopulmonary exercise testing (CPET).

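### No stated test compares the exercise change with the control change: the only outcome analysis is a before/after test within each period

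*Protocol article*

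**What the plan says.** Study Design: "This study is a prospective single-center randomized cross-over controlled trial". Randomization gives the two sequences: "Group A will start with the tailored intervention after a control period of 6 weeks", and "Group B will start the tailored intervention immediately after the first measurement moment". It then gives the control its role: "Group A serves as controls for the whole group (with a 2:1 ratio) as group A does not have a washout period". The Intervention section sets the length of training: "All children will participate in two or three supervised training sessions a week for 12 consecutive weeks".

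Statistical Analysis names one method for outcomes: "Differences before and after the control or exercise period will be analyzed using a paired T-test for normally distributed data", with the Wilcoxon signed-rank test as the non-normal alternative. The only between-group tests are for another purpose: "Baseline characteristics between groups will be compared with the unpaired student's T-test for normally distributed data", plus Mann-Whitney and chi-squared tests for the same baseline comparison. No contrast between conditions and no period or sequence term is stated.

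Sample Size Calculation bases power on the change in peak VO2 after the intervention. It uses a 5% rise, SD 2.19, 80% power and alpha 0.05, and enters no control change.

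**The concern.** The randomisation gives group A a control period that can be set against group B's intervention period. That contrast is what separates training from growth, familiarity with the test and season. A before/after test on the exercise period cannot make the separation, because it counts all of them as effect. A second before/after test on the control period does not repair this: two separate p-values are not a test of their difference. The comparison is also lopsided, since all children supply an exercise change and only about half supply a control change.

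The crossover label hides a further point. Only group A has a control period, and it always precedes that group's training, so within group A condition and order are confounded. The contrast protected by randomisation is group B's first-period change against group A's control change. At stake is whether the primary result is a controlled estimate or an uncontrolled one reported under a controlled design.

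**Working it through.** **1. Which test was the trial sized for?** Inputs, all from Sample Size Calculation: peak VO2 of 27, 39, 37.7 and 36 mL/kg/min for Fontan, BPD, Pompe and IBD; a 5% rise; SD 2.19; alpha 0.05 (taken as two-sided); power 80%.

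Paired formula: n = ((1.96 + 0.84) × 2.19 / δ)², computed with unrounded normal quantiles. A two-sample comparison needs twice that per arm.

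| Group | δ (5%) | Paired n | Stated n | Two-sample n per arm |
|---|---|---|---|---|
| Fontan | 1.35 | 20.7 | 21 | 42 |
| BPD | 1.95 | 9.9 | 10 | 20 |
| Pompe | 1.885 | 10.6 | 10 | 22 |
| IBD | 1.80 | 11.6 | 12 | 24 |

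The stated sizes follow the paired formula (Pompe to within one child) and not the two-sample one. Sizing and analysis therefore agree with each other, and both are uncontrolled.

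**2. The exercise-period test alone, with drift and no training effect.** Noncentral t, stated n, SD of change 2.19. The probability of a significant rise, against a nominal 2.5%, is:
- 1% drift: 7-8%
- 2% drift: 16-19%
- 3% drift: 31-37%
- 5% drift: 68-77%

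**3. Reading the two paired tests side by side.** Assumptions: exercise n = 21/10/10/12, control n = 10/5/5/6, SD of change 2.19, independent periods, the same drift in both, no training effect. The probability that the exercise test is significant and the control test is not is P(exercise significant) × (1 − P(control significant)), with two-sided tests.

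| Drift | Fontan | BPD | Pompe | IBD |
|---|---|---|---|---|
| 0.25 mL/kg/min | 7% | 6% | 6% | 6% |
| 0.5 | 15% | 9% | 9% | 10% |
| 1.0 | 38% | 22% | 22% | 26% |
| 5% of baseline | 45% | 47% | 46-47% | 46% |

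Example, Fontan at 1.0: 0.513 × (1 − 0.25) = 0.38.

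If drift instead builds up with time, so that the 6-week control carries half of the 12-week drift, the range becomes 24-46% at 1.0 and 60-66% at 5%.

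**4. Power of the controlled contrast.** Two-sample t-test of group B's intervention change against group A's control change, with the 5% target as the difference and 2.19 as the SD of change:
- By diagnosis, stated evaluable numbers split in half: Fontan 27%, BPD 24%, Pompe 22%, IBD 25%.
- By diagnosis, all 72 children and no dropout (14, 7, 7 and 8 per arm): 35%, 33-34%, 32%, 33%.
- Pooled, for an assumed difference of 1.65: 77% with 26 against 27 (the 53 evaluable children) and 88% with 36 against 36. The value 1.65 is close to the enrolment-weighted mean of the four targets: (28 × 1.35 + 14 × 1.95 + 14 × 1.885 + 16 × 1.80) / 72 = 120.29 / 72 = 1.67.

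**The case against.** The best defence is that a controlled comparison is plainly intended: Randomization says group A supplies the controls, the data would largely allow the comparison, and a condensed article may leave the model to a fuller plan. Part of this stands. A reader might infer that no training effect can be attributed, or that the randomisation adds nothing. The document does not support either, because the intent is stated and the first-period contrast is available. What remains is that the article does not leave the outcome analysis open. It names a within-period test, assigns unpaired tests to baseline only, and is sized on the same basis.

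A reader might also infer that efficacy will be claimed when the exercise test is significant and the control test is not. The document states no such rule, so the side-by-side percentages illustrate a risk and are not the trial's error rate. They also rest on inputs the document does not give. It states no untreated drift and does not say that 2.19 is an SD of change. Independence is only approximate, because group A contributes to both periods and the visit that ends its control period starts its training. At small drifts (0.25-0.5) the false pattern is only 6-15%.

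Finally, the controlled contrast has its own weakness: it sets 12 weeks against 6, so time-dependent drift would still favour exercise. That limits what the contrast can show, but it does not favour the uncontrolled test.

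**Conclusion.** The point holds in this form: no stated test compares exercise change with control change, although the trial is presented as randomised and controlled, and the sample sizes are those of a paired before/after test. Followed as written, the analysis reads untreated drift in peak VO2 as training effect. How large the error would be depends on a drift that the document does not quantify. Over the range shown, the misleading pattern runs from about 6% to 47% with equal drift, given an SD of change of 2.19, half as many controls and independent periods. The 80% power belongs to the before/after test only. By diagnosis, the controlled contrast has roughly 22-35% power if 2.19 is the SD of change.

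**What to change.** Make the primary analysis the exercise-minus-control difference in peak VO2 change, with a 95% CI, pooled over diagnoses. Either of two forms would do:
- a baseline-adjusted ANCOVA of the randomised first period (group B intervention against group A control), adjusted for diagnosis; or
- a mixed model over the pre/post visits, with child as random effect and period, condition and diagnosis as fixed effects. Baseline must not be entered as both outcome and covariate.

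The mixed model should not be expected to rescue power. Once a period term is included, group A's second period goes mostly to estimating that term, and any gain depends on a within-child correlation that the document does not give.

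Report diagnosis-specific estimates with intervals as secondary, and keep the paired tests as descriptive. Describe the design as randomised delayed-start. State that the 6-week control against the 12-week intervention limits the contrast. Restate that the 80% power refers to the paired test, and give the power of the controlled contrast, pooled and by diagnosis.

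Reconcile the visit schedule as well. Study Design gives group A two identical visits and a follow-up, and group B three identical visits. Under Randomization, group A is the group that needs assessments before control, between control and training, and after training. Until this is settled, it is not certain that the control change is measured in the intended group.

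The cost is analysis wording, a design label and a less favourable stated power by diagnosis.

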### Sample Size Calculation

The power calculation is based on the primary study outcome of change in peak VO_2_ after the tailored intervention. As reported peak VO_2_ in literature is different for every patient group, the group size needed to observe an increase in peak VO_2_ of at least 5%, which is clinically relevant, is different for each diagnose.

Fontan group size calculation: Previous studies show that children with a single-chamber heart have a Peak VO_2_ of 27 ml/kg/min (23). The difference of a 5% increase in Peak VO_2_ can be observed with a power of 80% and an alpha of 0.05 in 21 children with a unicameral heart assuming a standard deviation of 2.19 VO_2_/kg (24).

*BPD Group Size Calculation*: Average children with BPD have a VO_2max_ of 39 ml/kg/min (25). An improvement in VO_2max_ of at least 5% is considered clinically relevant. The difference of an increase in VO_2max_ of 5% can be observed with a power of 80% and an alpha of 0.05 in a sample of 10 children with BPD, assuming a standard deviation of 2.19 VO_2_/kg (24).

*Pompe Group Size Calculation*: The only previous study investigating exercise capacity in children with Pompe disease includes five patients and shows that children with Pompe have a PeakVO_2_ between 11.1 and 40.2 ml/kg/min, with a 75%ile of 37.7 ml/kg/min (14). We have chosen to use the 75%ile to calculate the group size, as we think this value of PeakVO_2_ is closest to the PeakVO_2_ of our own Pompe children population. An improvement in PeakVO_2_ of at least 5% is considered clinically relevant. The difference of a 5% increase in PeakVO_2_ can be observed with a power of 80% and an alpha of 0.05 at a number of 10 children with Pompe disease assuming a standard deviation of 2.19 VO_2_/kg (24).

*IBD Group Size Calculation*: In previous studies, untrained children with IBD had an average peak VO_2_ of 36 ml/kg/min (19). Twelve IBD patients will be needed in order to observe an increase in peak VO_2_ of at least 5%, which is clinically relevant, with a power of 80% and an alpha of 0.05 based on a standard deviation of 2.19 VO_2_/kg (24).

Anticipated on a dropout rate of 30–40% at 16 patients with IBD, 14 patients with Pompe disease, 28 patients with a Fontan circulation and 14 patient with PBD will be included.

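### Wrong as written: the only effect test stated is a before-after change within each period, with no exercise-versus-control contrast, in a trial described as randomised and controlled

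*Protocol article*

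**What the plan says.** Study Design presents the trial as controlled: "This study is a prospective single-center randomized cross-over controlled trial". Randomization gives the control role to one arm: "Group A serves as controls for the whole group (with a 2:1 ratio) as group A does not have a washout period". It also fixes that arm's order: "Group A will start with the tailored intervention after a control period of 6 weeks". The other arm starts exercise straight after its first measurement.

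Statistical Analysis then names one method for effects: "Differences before and after the control or exercise period will be analyzed using a paired T-test for normally distributed data", or a Wilcoxon signed-rank test for non-normal data. Its only between-group methods (unpaired t, Mann-Whitney, chi-squared) have a different job: "Baseline characteristics between groups will be compared with the unpaired student's T-test for normally distributed data". The analysis set is stated as well: "A per protocol analysis will be used". No method is named for comparing change under exercise with change under control.

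Sample Size Calculation follows the same before-after logic: "The power calculation is based on the primary study outcome of change in peak VO_2_ after the tailored intervention". It asks for 21 Fontan, 10 BPD, 10 Pompe and 12 IBD children, for a 5% rise at 80% power, alpha 0.05 and SD 2.19. Enrolment is 28, 14, 14 and 16.

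**The concern.** A paired test of the exercise period asks whether peak VO2 changed, not whether it changed more than it would have without training. The primary outcome comes from a test ridden to exhaustion, neither children nor physiotherapists are blinded, the test is repeated, and the children are growing. A retest, motivation or growth effect would therefore be counted as a training effect.

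Running a second paired test on the control period does not solve this. A significant change in one period beside a non-significant change in the other is not a test of their difference. The control period also has only about half the children, so its test is the less sensitive of the two.

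The exercise-period data mix test orders too. Exercise-first children start that period from their first CPET, whereas control-first children have already been through a control period.

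**Working it through.** **Inputs, from Sample Size Calculation.** Mean peak VO2 is 27 (Fontan), 39 (BPD), 37.7 (Pompe) and 36 (IBD) ml/kg/min. A 5% rise is therefore 1.35, 1.95, 1.885 and 1.80. SD is 2.19. Sidedness is not stated, so two-sided alpha 0.05 is assumed.

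**Step 1: which test was the trial sized for?** One-sample formula: n = ((1.96 + 0.84) × 2.19 / delta)². Two-sample formula: twice that, per arm.

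| | Stated n | One-sample n | Two-sample n per arm |
|---|---|---|---|
| Fontan | 21 | 20.7 | 42 |
| BPD | 10 | 9.9 | 20 |
| Pompe | 10 | 10.6 | 22 |
| IBD | 12 | 11.6 | 24 |

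The stated sizes match the one-sample formula (Pompe rounds to 11 against the stated 10). They do not match the two-sample formula, per arm or in total. So 2.19 was used as the SD of a change, and that change was set against zero.

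**Step 2: what an untreated gain does to the exercise-period test.** Assume no training effect and an untreated gain g in every child. The documents give no value for g. The one-sample t-test has n − 1 degrees of freedom and noncentrality g × mean × √n / 2.19. For Fontan at g = 2% this is 0.54 × √21 / 2.19 = 1.13. Probability of a significant result in favour of training:

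| Assumed gain | Fontan | BPD | Pompe | IBD |
|---|---|---|---|---|
| 0% | 2.5% | 2.5% | 2.5% | 2.5% |
| 1% | 8% | 7% | 7% | 8% |
| 2% | 19% | 17% | 16% | 18% |
| 3% | 37% | 33% | 31% | 35% |

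If a 3% gain is purely a first-retest effect, only the exercise-first half carries it into the exercise period. The average gain is then 1.5%, and the probability is 11-12.5% per disease.

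Downward drift works the other way. With a true 5% effect and a 2% untreated fall, the net change is 3%, so by the last row the test detects it in only 31-37% of trials.

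**Step 3: the two paired tests side by side.** Take the same gain in both periods, half the children in the control period, and the periods as independent. The pattern of exercise significant and control not significant then arises in 15-17% of trials per disease at 2%, and 26-30% at 3%.

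**Step 4: power of a real contrast for a 5% effect.** SD of change is 2.19 in each arm.

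- Pooled, 53 completers: mean effect (21 × 1.35 + 10 × 1.95 + 10 × 1.885 + 12 × 1.80) / 53 = 1.67. With 26 v 27 and 53 − 5 = 48 degrees of freedom (arm and diagnosis fitted), power is 77%.
- Pooled, all 72: mean effect 1.67, 36 v 36, 67 degrees of freedom, power 89%.
- Single disease, stated completers split 1:1: 27% (Fontan), 24% (BPD), about 22% (Pompe), 25% (IBD).
- Single disease at 80% power: 84, 40, 44 and 48 children in total.

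Baseline adjustment multiplies the variance by (1 + r)/2. That is 0.90-0.95 if the before-after correlation r is 0.8-0.9 (an assumption), so these powers are slightly conservative.

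**The case against.** The strongest defence is that this is a short methods paragraph in an article. Randomization makes the control role explicit, so a controlled comparison is plainly intended, and the full protocol or analysis plan may name it. A reader might infer that the trial never compares exercise with control and wastes its randomisation. The documents do not support that. They show only that the effect test stated here is within-period and does not match the design. That narrower point stands, because the article does not leave the method open: it names one, and the sizing agrees with it.

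The sentence might also be read as pairing each child's control change with the exercise change. The wording does not say so, and only control-first children have both periods, so the others would contribute no pair.

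A second objection concerns size, and it holds in part. The drift is assumed and its direction is unknown. Peak VO2 per kg already removes some of the effect of growth, and the Introduction describes Pompe disease as progressive, so drift there could be downward. The 31-37% is a what-if, not an estimate of this trial's error rate.

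A third objection concerns the remedy, and it also stands. Control lasts 6 weeks, while exercise is set out as "All children will participate in two or three supervised training sessions a week for 12 consecutive weeks", so a contrast removes a shared retest effect but only part of any drift that grows with time. Pooling averages four separately designed interventions, which is a choice of question rather than a correction. Study Design gives group A two visits and a follow-up and group B three, which conflicts with Randomization placing the control period in group A.

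**Conclusion.** The stated analysis is wrong for the stated design and must be changed. What the documents establish is the mismatch: a randomised controlled design, with an effect test and a sample size that are both uncontrolled before-after. The 80% per-disease power therefore applies only to a change against zero (68-77% if computed with the t distribution at the stated numbers). It does not apply to an exercise-versus-control difference.

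The size of the bias depends on drift that the documents do not give. The false-positive figures rest on an SD of change of 2.19, the stated completer numbers and a uniform upward gain. They fall if the gain is confined to first retests, and they turn into lost sensitivity if drift is downward. The powers of the contrast rest on the same SD in both arms and a 1:1 split.

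**What to change.** In Statistical Analysis, replace the effect sentence with one primary contrast:

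- Make the primary inference the exercise-minus-control difference in change in peak VO2. Compare the exercise-first sequence's exercise period with the control-first sequence's control period, by ANCOVA adjusted for baseline peak VO2 and diagnosis, with a 95% CI.
- Report disease-specific differences from a diagnosis-by-condition term. Say openly that the pooled estimate averages four different interventions. If disease-specific effects are to be primary, say that too and accept the lower power.
- Keep the within-period paired tests as descriptive, and base no claim of effect on them.
- Name the arms by sequence rather than letter until the visit schedules in Study Design and Randomization are reconciled.
- State that the periods last 6 and 12 weeks, so time-dependent drift cancels only in part.
- In Sample Size Calculation, restate power for the contrast: about 77% pooled with 53 completers (89% with 72), and about 22-27% per disease.

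**Cost.** No new measurements are needed. The price is a wider interval than a one-sample change gives, and giving up the claim of 80% power in each disease. Regaining that claim for a controlled comparison would take 84/40/44/48 completing children (Fontan/BPD/Pompe/IBD) in place of 21/10/10/12.
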